### Trial design

The CHARIOT trial is a hybrid type 1 effectiveness-implementation study using a non-blinded RCT design with two parallel treatment arms. Participants who are PWID and who have a non-reactive result on rapid HIV test will be randomly assigned to either *C-THR* with telehealth services for HIV prevention (syringes, PrEP, MOUD) and treatment of HCV, STIs, and skin and soft tissue infection (SSTIs) that can be accessed wherever the patients are (e.g., SSP, mobile unit, outreach at homeless encampment, shelter, or patient home); or, to non-SSP clinic referral with support from a patient navigator for first clinic visit for PrEP, MOUD, treatment of HCV, STIs, and SSTIs. Randomization will occur by permuted block with stratification for site (fixed vs. mobile) and OUD (yes vs. no). An implementation process evaluation and cost-effectiveness analysis will also be performed. The study protocol (version 1.0) follows the Standard Protocol Items: Recommendations for Interventional Trials (SPIRIT) Statement.

## Methods: participants, interventions and outcomes

### Study setting

Miami is an ideal city for studying *C-THR* in the context of an SSP. The IDEA Miami SSP was authorized in 2016 as the first legal SSP in Florida. There are currently over 2200 PWID enrolled, with 9% testing reactive for HIV (10.4% at the mobile site, 8.2% at the fixed site) and 41% for HCV (51.1% at the mobile site, 39.0% at the fixed site) through our routine every 3 months opt-out HIV/HCV screening algorithm [24]. Miami-Dade County is a high priority county under the Ending the HIV Epidemic initiative [1] and has a high prevalence of PWID with estimates ranging from 7607 to 10,529 [50, 51]. IDEA Miami is housed within an academic medical center (the University of Miami) in partnership with one of the largest safety-net hospitals in the country (Jackson Health System), and is supported by major research centers including the NIH-funded Miami Center for AIDS Research and NIH-funded Center for HIV and Research in Mental Health. IDEA Miami exchanges over 30,000 syringes per month and operates one fixed site and five mobile sites in both the downtown area as well as rural agricultural areas in Miami-Dade County.

### Eligibility criteria

Eligibility criteria include the following: (1) age 18 or older; (2) able to speak English or Spanish; (3) willing and able to sign informed consent, provide locator information and medical records release; (4) non-reactive result on rapid HIV test; (5) use of SSP to exchange syringes two times in the past 3 months; and (6) planning to stay in the area for 12 months. Of note, pregnant people are eligible for enrollment in this trial but will not be purposely recruited.

Exclusion criteria include the following: (1) PWID with HIV; (2) currently on MOUD; (3) currently on PrEP; (4) principal or site investigator discretion; (5) currently in prison or jail; and (6) current enrollment in NIDA Clinical Trials Network (CTN) 121 which is a study that our team is leading in Miami to test a comprehensive, integrated hospital-based intervention to address concurrent treatment and follow-up support for PWID with severe infections; (7) current enrollment in M2HepPrEP (R01 DA045713) [52] which is an integrated Hepatitis C and HIV prevention study that our team is completing this year; (8) hepatitis B surface antigen positive; (9) receipt of *THR* in the previous 3 months; and (10) signs or symptoms of acute HIV infection. Investigator discretion could include serious medical, psychiatric, or co-occurring SUD that acutely requires a higher or different level of care including the following: (1) disabling or terminal medical illness (e.g., decompensated heart failure); (2) severe, untreated or inadequately treated psychiatric condition (e.g., active psychosis); (3) in need of medical detoxification for severe alcohol, benzodiazepine, or other depressant or sedative hypnotic use; (4) suicidal intent or plan; and (5) homicidal ideation.

### Who will obtain informed consent?

Study staff including the study coordinator, research assistant, and peer counselor will recruit participants and obtain informed consent. Screening informed consent will be obtained at the SSP fixed site or mobile sites after a participant has screened non-reactive for HIV. The main informed consent will be obtained after a participant is determined to be eligible for the study.

### Additional consent provisions for collection and use of participant data and biological specimens

Individuals who meet preliminary screening criteria (i.e., that the participant is a current SSP client with a non-reactive HIV rapid test) will be requested to complete the screening informed consent process including medical record release, a fourth generation HIV test, hepatitis serologies and HCV RNA, 3-site gonorrhea and chlamydia testing, syphilis screening, comprehensive metabolic panel, complete blood count, urine drug screen, urine pregnancy test (if applicable), and a urine tenofovir test. Consent for screening will be obtained by study staff using an institutional review board (IRB)-approved written consent form.

For individuals who meet the full eligibility criteria and would like to enter the study, informed consent will be obtained by study staff using an IRB-approved written consent form in English or Spanish agreeing to the possibility of telehealth with wraparound services for possible PrEP, MOUD, and treatment of HCV, STIs or SSTIs. They will also be required to provide locator information including phone number, email, social media accounts (e.g., Facebook, Instagram, Linkedin) and friend/family contact information and medical records release. Participants will receive a copy of all consent documents.

No additional studies are planned at this time.

## Interventions

### Explanation for the choice of comparators

The CHARIOT study is proposed as an efficacy trial because the study team has already demonstrated the feasibility and acceptability of telehealth for rapid antiretroviral (ART) initiation among PWID and is currently conducting the T-SHARP trial to determine the efficacy of telehealth for HIV care among PWID [40]. *C-THR* will be based out of the IDEA Miami SSP due to its established relationship of trust within the PWID community, and all study participants will be registered clients of the SSP. The study will be a randomized 2-arm trial with participants randomized to either C-*THR* with enhanced telehealth services for PrEP, MOUD, and treatment of HCV, STI or SSTI that can be accessed where the patients are (e.g., SSP, mobile unit, outreach at homeless encampment, or patient home) or to non-SSP clinic referral with a patient navigator. Recruitment will take place at the IDEA Miami SSP and participants will be assessed at 3, 6, 9, and 12 months following randomization to measure PrEP engagement (tenofovir on DBS or abstraction of cabotegravir injection records) or MOUD engagement (norbuprenorphine or methadone on UDS; or abstraction of naltrexone or buprenorphine injection records), as well as syringe coverage, PrEP adherence, HCV treatment engagement, HCV cure, time to injection-related harm and number of injection-related harms. Quantitative assessments will help estimate predictors of engagement in HIV prevention services via the C-*THR* intervention package. Just as with our T-SHARP trial, it is expected that syndemic factors [53, 54] such as unstable housing and/or food insecurity will impact engagement in HIV prevention services across time points and that the C-*THR* intervention will perform better at mitigating the effects of these potential confounders.

### Intervention description

#### C-THR intervention arm

Component 1 of the *C-THR* intervention utilizes telehealth technology facilitated by a peer counselor to connect participants to on-demand visits with a study physician and clinical psychologist. Technology is available wherever the participant is located and prefers engagement (e.g., SSP, home, shelter, encampment) via a HIPAA-compliant videoconferencing application, iPads, and headphones for privacy. All study physicians practice medicine through a harm reduction lens and are experienced in HIV prevention and the treatment of SUD. A call schedule across the study physicians will support on-demand access for participants. By incorporating enhanced access to a clinical psychologist, the *C-THR* intervention will also be capable of addressing the estimated 40% of people with SUD who have co-occurring mental health disorders [55] (e.g., post-traumatic stress disorder, depression and anxiety) as well as the participants who have stimulant use disorders. The psychologist will formulate a treatment plan and visit frequency with study physicians as determined by clinical indication(s), and will provide ongoing services including talk therapy and psychotropic medications to address concurrent mental health disorders. This essential component will allow for an evidence-based approach to co-occurring stimulant use disorders which are prevalent in the Miami PWID community [56] to augment emerging pharmacotherapies [57–60].

On-site, culturally appropriate blood draws will be performed at the SSP fixed or mobile sites by a medical assistant/phlebotomist and sent to the lab for testing. Blood will be sent to LabCorp to measure creatinine, and to the Department of Health to be tested for HIV, viral hepatitis, and STIs. The medical assistant/phlebotomist will swab the participants’ throats to test for gonorrhea and chlamydia and will instruct the participants on how to collect a self-swab for rectal gonorrhea and chlamydia in a private bathroom. Urine will be collected for gonorrhea and chlamydia screening, as well. Finally, point-of-care urine tests will assess the presence of buprenorphine or tenofovir.

Component 2 of the *C-THR* intervention utilizes SSP-based peer counselors who will work with the physicians and clinical psychologist to evaluate the participants and encourage them to initiate and remain in care using motivational interviewing based techniques. If indicated and desired, PrEP, MOUD, direct-acting antivirals (DAA) for HCV, and/or antibiotics for STI/SSTI will be prescribed by the physician. The study will not directly fund medications; rather, peer navigators and physicians will assist in securing access to therapies using the participant’s health insurance, county health system indigent care funds, or other available grants and sources. Prescribed medications will be picked up from the pharmacy by the peer counselor, or, in the case of antibiotics, immediately dispensed from the SSP. Participants will enroll in a weekly medication management schedule with medication storage via pill lockers available at the SSP. Participants will be able to choose between accessing their medications at the SSP or having them delivered by the peer counselor during routine engagement visits. Peer counselors will explore barriers to medication adherence with a focus on the importance of adherence and safe injection practices for positive health outcomes and will work to enhance participants’ self-efficacy and support overall wellbeing. Intensive wrap-around support from the peer counselors and digital technology will help us assist the participants in other domains such as housing, food insecurity, and insurance (essential to cover the cost of PrEP/DAA) and provide an opportunity for routine motivational interviewing from the integrated care team. Peer counselors will ideally be persons with the lived experience of SUD, mental health disorders, and/or trauma. All *C-THR* team interactions with participants will be culturally sensitive, non-stigmatizing and non-judgmental, grounded in respect and mutual aid. *C-THR* also provides needs-based access to syringes and naloxone alongside the delivery of PrEP and MOUD services.

Bringing the mobile telehealth technology along with the exchange of syringes to participants will allow us to overcome previously reported barriers to the use of telehealth among PWID, including lack of access to mobile phones [61–63]. A limitation to the intervention is that not all medical care can be delivered remotely via telehealth. For medical care that cannot be offered at the IDEA Miami SSP or remotely in the *C-THR* arm (e.g., x-ray, dental extraction), peer counselors will navigate participants to appropriate free care within the academic safety-net health systems. Not every service component of the intervention will be delivered via telehealth (e.g., provision of syringes), and in-person engagement with the peer counselor is an essential component of the *C-THR* intervention.

The *C-THR* intervention manual will be adapted from the *THR* intervention manual currently being used in the T-SHARP trial via consultation with the IDEA Miami SSP staff, program participants and the Florida Harm Reduction Collective Community Advisory Board. Participants in the *C-THR* arm will have all intervention sessions (i.e., physician, psychologist and peer counselor encounters) audio recorded. Participants will be given the option to opt out of audio-recording.

At the end of the 12-month study period, participants randomized to the *C-THR* arm will be offered continuation in the *C-THR* intervention.

### Non-SSP clinic referral and patient navigation arm

Participants who are randomized to non-SSP clinic referral and patient navigation (i.e., the control condition) will receive the current linkage to care protocols at the IDEA Miami SSP including case management/social work services through our community engagement team. This team is comprised of case managers and social workers and provides the wraparound support needed to navigate the fragmented healthcare system in Miami. The team will assist participants in scheduling appointments at community health clinics including FQHCs or the safety-net Jackson Health System. The community engagement team provides active clinic referral—that is, a member of the team accompanies participants to their first clinic visit. The staff can provide transport in the mobile van or use ride-share (e.g., Lyft Healthcare) to actively link participants to registration, phlebotomy, and pharmacy services. This model of patient navigation has helped PWID achieve rapid HIV viral suppression at our SSP [7].

The community engagement team will work to link to non-SSP clinics that offer PrEP, MOUD, treatment for HCV/STI/SSTI, and/or mental health services based on participant needs to promote parallel access to care between the two arms. Crossover could occur if participants in the *C-THR* group receive services at a community health center; however, in our experience, PWID receiving services at the IDEA Miami SSP rarely independently seek out services at community health centers. Conversely, telehealth could occur in the control arm, but this would not be facilitated in the specific non-stigmatizing environment of an SSP and peer counselors would not bridge the digital divide, facilitating and motivating care seeking behaviors in participants. We will include questions on follow-up assessments that will be able to ascertain crossover in use of services.

At the end of the 12-month study period, participants randomized to the non-SSP clinic referral and patient navigation arm will be offered entry into the *C-THR* intervention.

### Criteria for discontinuing or modifying allocated interventions

There will be no special criteria for discontinuing or modifying allocated interventions.

### Strategies to improve adherence to interventions

In order to assure fidelity to the C-*THR* intervention, all intervention sessions (i.e., physician, psychologist, and peer counselor encounters) will be audio recorded. Participants will be given the option to opt out of audio-recording. Ten percent of the audio-recorded intervention sessions will be reviewed by the study clinical supervisor(s) and intervention developers for implementation fidelity monitoring purposes and also to provide ongoing clinical feedback to the study staff.

### Relevant concomitant care permitted or prohibited during the trial

Participants must agree to the possibility of receiving telehealth-enhanced access to HIV prevention services via the IDEA Miami SSP. However, that does not preclude them from engaging with other HIV/AIDS service organizations, primary care providers, or substance use treatment programs for further support.

### Provisions for post-trial care

After study completion, participants in both arms will be offered the *C-THR* intervention.

### Outcomes

Table 1 shows the primary and secondary outcomes of objective 1. The co-primary outcomes will be engagement in HIV prevention via PrEP and/or via MOUD. PrEP engagement will be measured by intracellular levels of TFV-DP on DBS or abstraction of a cabotegravir injection in the previous 8 weeks. MOUD engagement will be measured by norbuprenorphine or methadone on UDS or abstraction of a naltrexone or buprenorphine injection in the previous 4 weeks.

**Table 1 Tab1:** Primary and secondary outcomes for objective 1

	Definition	Measure
Primary outcome		
HIV Prevention via PrEP	Taking PrEP at 3-, 6-, 9-, and 12-month follow-up	Intracellular levels of tenofovir diphosphate (TFV-DP) by DBS or cabotegravir injection in previous 8 weeks by electronic health record abstraction
HIV Prevention via MOUD	Taking MOUD at 3-, 6-, 9-, and 12-month follow-up	Norbuprenorphine or methadone on UDS or naltrexone or buprenorphine extended-release injection in previous 4 weeks by electronic health record abstraction
Secondary outcomes		
Syringe coverage	Dispensing syringes to cover each injection event	Number of syringes distributed/(number of injections per day × days between exchanges) from SSP administrative data
PrEP Adherence	Taking PrEP at least 4 times per week	TFV-DP level of 700 fmol/punch on DBS for TDF [64]; TFV-DP level of 950 fmol/punch on DBS for TAF[65]
Engagement in HCV treatment	Receiving a prescription for DAA	DAA prescsiption confirmed on electronic health record abstraction
HCV cure (SVR 12)	Initiating HCV treatment and achieving undetectable HCV RNA PCR at least 12 weeks after completion of therapy	Negative HCV RNA PCR (viral load) at least 12 weeks post treatment completion
Treatment of STIs	Receiving treatment for STI after a positive screen	Prescription of appropriate antibiotics (may differ based on allergies) from electronic health record abstraction
Time to harm	Time to: (1) emergency department visit or hospitalization for injection-related infection or overdose; (2) incident HIV infection; (3) incident HCV infection; or (4) death from overdose	(1) Electronic health record abstraction; (2, 3) IDEA test results; (4) electronic health record abstraction or medical examiner database
Number of harms	Count of (1) emergency department visit or hospitalization for injection-related infection or overdose; (2) incident HIV infection; (3) incident HCV infection; or (4) death from overdose	(1) Electronic health record abstraction; (2, 3) IDEA test results (4) electronic health record abstraction or medical examiner database

Secondary analyses will evaluate positive health behaviors by counts per person per study arm. PrEP adherence will be defined as taking PrEP at least four times per week for men and at least 6 times per week for women as confirmed by TFV-DP levels on DBS. HCV treatment engagement will be defined as receipt of a prescription for DAA. HCV cure will be defined as sustained virologic response at least 12 weeks after completing DAA (SVR 12) and treatment of STIs is defined as receipt of the appropriate antibiotic treatment after diagnosis. Secondary outcomes will also evaluate negative health outcomes or harms by counts per person per study group. Emergency department visits or hospitalizations will be confirmed by participants’ consent for records release and abstraction from Miami area hospitals which have integrated electronic health records. Incident HIV and HCV infections (or reinfections) will be confirmed by positive 4th generation HIV antigen/antibody test and detected HCV RNA, respectively. Death from overdose will be confirmed by hospital record, Miami-Dade County Medical Examiner database search or direct inquiry with the medical examiner. In addition to counts, time to secondary outcomes, both positive and negative, will be compared by study arm.

For objective 2, the primary health economic outcomes will be: (1) implementation and ongoing management costs of the two healthcare models, and (2) short-term cost-effectiveness from the perspectives of the healthcare sector and society. The primary economic outcome will be the incremental cost-effectiveness ratio (ICER) from the healthcare sector and modified societal perspectives. The measure of effectiveness will be quality-adjusted life years (QALYs) and incident HIV infections averted.

For objective 3, the process evaluation will focus on contextual factors and strategies related to achieving the following implementation outcomes: (1) reach, (2) efficacy, (3) implementation (cost, fidelity, and adaptation), and 4) maintenance (Table 2). The “Reach” metric will be operationalized according to the RE-AIM guidelines [66] to understand the representativeness of individuals being recruited and enrolled into the trial compared to the general SSP population. “Implementation” outcomes that will be assessed include: acceptability (provider and staff level) according to the Theoretical Framework of Acceptability (TFA) [67] intervention appropriateness (provider and staff level), measured by the Intervention Appropriateness Measure (IAM) [68], implementation fidelity, and feasibility (participant level). The conceptual distinction of these outcomes are specified by Proctor’s taxonomy of implementation outcomes [69] (Table 2).

**Table 2 Tab2:** Implementation outcomes for objective 3

Construct	Measure	Data source
RE-AIM implementation evaluation framework		
Reach	Proportion of eligible participants in SSP engaged in the intervention	SSP administrative records
Efficacy	Efficacy of the *C-THR* model on engagement in HIV prevention	Study Aim 1
Adoption	N/A	N/A
Implementation	PRISM Constructs (i.e. external environment, patient perspective)	Interviews with providers, SSP staff, and participants
Maintenance	Cost analysis, cost-effectiveness, long-term simulation modeling	Study Aim 2

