### Plans to promote participant retention and complete follow-up

Participants will be recruited from the IDEA Miami SSP by our racially and ethnically diverse staff that includes peer counselors. Due to the fundamental trust that the SSP has within the community of PWID, we anticipate that utilization of the harm reduction approach of meeting potential participants where they are will support ongoing recruitment into the trial due to the benefits of participation (including telehealth access to a physician, psychologist, counselor). Study staff are experienced and trusted in the community of PWID, and our empowerment of peers as the true experts in PWID health will facilitate recruitment. Providers can remain permanent after trial conclusion since stigmatization continues to be omnipresent in the traditional healthcare system. In our *THR* for PWID with HIV pilot (n = 35), all PWID continued to receive HIV primary care via *THR* after the pilot, even when no longer utilizing syringe services. Since all participants will be recruited via the SSP, the routine exchange of syringes and street outreach will ensure ongoing contact with all participants in the trial. Participants typically visit the program weekly and this ongoing distribution of harm reduction supplies will allow the study team to retain participants in the trial. In CTN-67 CHOICES, of 47 randomized patients with HIV and OUD at the University of Miami site, we retained 45 (96%) at 12-month follow-up. We also plan to use a locator form that we have used in other CTN studies and that will be reviewed by our community advisory board. Based on previous published studies regarding HIV prevention among PWID and to ensure we obtain adequate power to detect an effect, we have powered the trial for 12-month retention rates of 66%.

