Though GEE estimates are consistent even if the correlation structure is misspecified, GEE's statistical efficiency improves as the working correlation structure more closely approximates the actual correlation structure [92], so various correlation structures suitable for the study's design will be considered (e.g., exchangeable, autocorrelated, *m*-dependent, unstructured) [93]. The QIC statistic will be used to select the final correlation structure [94]. Recruitment site (fixed site vs. mobile site) and OUD diagnosis (yes vs. no) will be included in all models as required by the stratified randomized design to obtain unbiased results [95]. Robust standard errors will be used to obtain correct inferences even if the chosen correlation structure remains slightly mis-specified. All analyses will include outlier and influential case screening via computation of GEE-based residual analysis, including leverage, DFBeta, and Cook’s D statistics [96]. If outliers are found, results will be reported with and without outliers included.

### Data analysis plan and statistical procedures to address secondary hypotheses of objective 1

We have proposed several secondary hypotheses related to the *C-THR* intervention. The secondary analyses will use exactly the same preliminary analysis and missing data strategy as Hypothesis 1. In secondary analyses, we will examine the distributions of syringe coverage, PrEP adherence, HCV treatment engagement, HCV cure, STI treatment uptake, and number of injection related harms and assess time to first injection-related harm between the intervention and control groups. GEE [92] will be used to perform the proposed secondary analysis, which is a planned time-averaged comparison of all post-baseline measurements of the each of these outcomes. Statistical procedures for these secondary hypotheses will follow the same strategy used for the primary hypothesis. The alpha will be set at 0.05 for each these secondary hypotheses. In each model, recruitment site (fixed site vs. mobile site) and OUD diagnosis (yes vs. no) will be included in these analyses as required by the stratified randomized design to obtain unbiased results. To maximize rigor, appropriate diagnostics including outlier and influential case screening will be examined for each model. If outliers are found, results will be reported with and without outliers included.

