### Methods in analysis to handle protocol non-adherence and any statistical methods to handle missing data

We will address any incomplete data with on of three approaches: multiple imputation [99], full-information maximum likelihood [87] or methods which include the expectations-maximization algorithm [86]. All of these approaches make the relatively mild assumption that incomplete data arise from a conditionally random (MAR) mechanism [100].

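### The Table 1 syringe-coverage ratio has no value once injecting or exchanging stops and becomes extreme when injecting is rare, so this secondary arm comparison can be distorted or selectively incomplete

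*Protocol article*

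**What the plan says.** Table 1 (Outcomes) lists syringe coverage as a secondary outcome of objective 1. The construct is "Dispensing syringes to cover each injection event" and the measure is "Number of syringes distributed/(number of injections per day × days between exchanges) from SSP administrative data". The section explaining the choice of comparators includes syringe coverage among the measures taken at 3, 6, 9 and 12 months.

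The section on the secondary hypotheses of objective 1 assigns these outcomes to GEE, "which is a planned time-averaged comparison of all post-baseline measurements of the each of these outcomes". It adds: "The alpha will be set at 0.05 for each these secondary hypotheses". Procedures are to follow those of the primary hypothesis, which is framed in odds. Only the harm count is given a different distribution and link, and time to first harm has its own test. Models will be screened for outliers, and results given both including and excluding any that are found.

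On incomplete data, the same section says: "The secondary analyses will use exactly the same preliminary analysis and missing data strategy as Hypothesis 1". The section on missing data says of the three candidate methods: "All of these approaches make the relatively mild assumption that incomplete data arise from a conditionally random (MAR) mechanism".

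The article states no cap, no threshold, no value for zero injections and no rule for a period with no further exchange. Questionnaires that cover injecting behaviour are scheduled only at baseline, 6 and 12 months.

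**The concern.** The construct asks whether injections are covered by a sterile syringe. The formula departs from it in three situations:

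- **No injecting.** The denominator is zero and the participant has no value. MOUD engagement is a co-primary outcome, so stopping is foreseeable in this trial.
- **Rare injecting.** The ratio climbs far above 1, although nothing above 1 means better cover of an injection.
- **No further exchange.** The interval runs from one exchange to the next, so it never closes after the last one. Someone who goes on injecting without new syringes is not scored as uncovered.

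Eligibility requires two exchanges in the previous 3 months, so the ratio should generally be computable at entry and can be lost afterwards. Whether a participant contributes, and with what value, then depends on injecting and programme contact after randomisation. Either may differ by arm. Methods that assume MAR do not repair this, because a person who does not inject has no underlying coverage value to impute.

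**Working it through.** The article gives no rate, threshold or power figure for syringe coverage, so there is no stated number to reproduce. The check evaluates the formula itself.

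**Inputs.** From the article: the Table 1 formula; a 7-day interval, from "Participants typically visit the program weekly" (section on retention); and 350 / 2 = 175 participants per arm. Assumed, and not in the article: 40 syringes per exchange, the injecting rates below, and the share of rare injectors.

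**Step 1: dependence on injecting rate.** Coverage = 40 / (injections per day × 7).

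| Injecting rate | Injections in 7 days | Coverage |
|---|---|---|
| 8 per day | 56 | 0.71 |
| 4 per day | 28 | 1.43 |
| 1 per day | 7 | 5.7 |
| 2 per week | 2 | 20 |
| 1 per week | 1 | 40 |
| none | 0 | undefined |

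**Step 2: influence on a mean, if a mean were used.** With 5% of an arm at 20 and 95% at 1.0, the mean is 0.05 × 20 + 0.95 × 1.0 = 1.95. Capped at 1.0, it is 0.05 × 1.0 + 0.95 × 1.0 = 1.0. This takes each of the 95% to be at 1.0. If they only averaged 1.0, the capped mean would be lower, but the 5% could still contribute no more than 0.05.

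**Step 3: after the last exchange.** Take 40 syringes and 4 injections a day, and close the open interval at an arbitrary date. The result is 40 / (4 × 7) = 1.43 at 7 days, 40 / (4 × 30) = 0.33 at 30 days and 40 / (4 × 90) = 0.11 at 90 days. The answer depends on a closing rule that the formula does not contain.

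**Step 4: illustrative simulation.** There were 2,000 runs of one arm of 175, with a 7-day interval, 10 to 40 syringes per exchange, regular injectors at 1 to 6 per day, and rare injectors at once a week or once in two weeks. All of these except the arm size and the interval are assumptions.

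| Stopped / rare | Mean (SD) | Median | No value | Proportion ≥ 1 |
|---|---|---|---|---|
| 0% / 0% | 1.45 (1.29) | 1.02 | 0% | 0.50 |
| 5% / 5% | 3.35 (9.18) | 1.10 | 5% | 0.53 |
| 10% / 10% | 5.46 (13.26) | 1.21 | 10% | 0.56 |
| 20% / 0% | 1.46 (1.29) | 1.03 | 20% | 0.50 |

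A few rare injectors dominate the mean, while the median and the proportion at or above 1 move little. Stoppers leave the mean almost unchanged because they are absent from it. A threshold therefore cures the unboundedness but not the missing values.

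**The case against.** Several counter-arguments carry weight.

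- **Condensed source.** This is one table cell in an article, and a full protocol or analysis plan may hold the derivation rules. That excuses silence on minor conventions. It does not excuse the formula, interval and data source that the article does state, which do not measure the construct beside them.
- **No mean is specified.** A reader might infer that arms will be compared on the average ratio. The article never says so. The primary strategy is framed in odds, and a threshold at 1 would fit the construct. The 1.95 is therefore conditional. Table 1 states no threshold, however, and one would not settle the zero and no-exchange cases.
- **Outlier reporting.** This tempers the extreme values, but it yields two answers, and the one without outliers may discard people who cut down. It does nothing for undefined values.
- **Needs-based supply.** C-THR provides syringes according to need, so a twice-weekly injector may not keep receiving 40 a week. The illustration is a stress case.
- **Scoring stoppers as covered.** This would mix cessation with syringe supply, so it is a choice of estimand and not a correction. That stands.
- **Absence from records.** Participants may use other service organisations, so no exchange here does not prove that injections went uncovered. That also stands, as a limit of the data source.

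A reader might also infer that the outcome drops the participants whom C-THR affects most, or that the bias favours one arm. The article supports neither. Engagement with PrEP alone need not change injecting, and no rates by arm are given. The retention section does report pilot participants staying in care after they no longer used syringe services, but that pilot enrolled people with HIV and gives no rate.

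**Conclusion.** The point holds as a flaw in the definition of one secondary outcome. By algebra alone, the Table 1 ratio is undefined at zero injections, unbounded as injecting approaches zero, and without a value after the last exchange. Nothing in the stated analysis or missing-data methods repairs this.

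The practical size and direction are unknown. The figures of 20 and 1.95 rest on 40 syringes per week, a 5% share of rare injectors and, for 1.95, an analysis of the mean, none of which the article states. The co-primary tests, their alpha and the sample size are untouched. Because coverage is tested between arms at 0.05 and the repair is cheap, the definition should be changed before any data by arm are seen.

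**What to change.** In Table 1:

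1. Replace the gap between exchanges with fixed windows between the 3-, 6-, 9- and 12-month assessments.
2. Analyse coverage per window as at least 1 versus below 1, or as a ratio capped at 1.0.
3. Count a window with reported injecting and no syringes distributed as not covered.
4. Report windows with no injecting as a separate category, with a pre-specified sensitivity analysis scoring them as covered.
5. For participants without exchange records, take injecting frequency from the 6- and 12-month questionnaires and limit their derivation to those windows. Alternatively, add one injecting item at the 3- and 9-month laboratory visits, which all participants are already due to attend.

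Item 5 is needed because the formula names only the programme's administrative records, and no questionnaire is scheduled at 3 or 9 months. It assumes that the injection-risk questions record frequency, which the article does not spell out.

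**Cost.** The change needs revised table wording, a revised derivation and possibly one extra question. Surplus syringes, such as those kept for others, earn no credit. Syringes obtained outside the programme remain uncaptured, so some windows scored as not covered will be misclassified.
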